#### Data management {19}

All data will be stored securely in an online database (i.e., REDCap). The investigators will be responsible for data registration and management. Data will be checked by at least two investigators.

#### Confidentiality {27}

Data from each patient will be assigned a code number, which will be the only link to patients’ identities during the trial period to maintain anonymity. Signed informed consent will be secured in a locked cabinet in a secure place in each hospital. Data will be stored for 3 years after trial completion according to the Enforcement Decree of the Bioethics and Safety Act of Korea. Data will be destroyed after 3 years; however, data storage may be extended with institutional review board (IRB) permission.

#### Plans for collection, laboratory evaluation, and storage of biological specimens for genetic or molecular analysis in this trial/future use {33}

Baseline and follow-up procedural laboratory test results and MRI images will be stored. There is no future research plan.

### Statistical methods

#### Statistical methods for primary and secondary outcomes {20a}

Parametric data will be reported as mean and standard deviation. Non-parametric data will be reported as median and range. Independent sample *t*-tests or Mann–Whitney *U* tests for continuous variables and chi-square or Fisher’s exact tests for categorical variables will be used to compare treatment groups. For the primary endpoint, rate of CR will be compared using a chi-square test. For secondary endpoints, Kaplan–Meier survival analysis and log-rank tests will be performed. A *p*-value < 0.05 will be considered statistically significant.

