## Introduction

### Background and rationale {6a}

Hepatocellular carcinoma (HCC) is the fifth most common cancer and the second leading cause of cancer-related mortality worldwide [1]. Although active surveillance programs and the widespread use of imaging have improved its early detection, HCC is often found at an advanced stage, and the outcomes of both local and systemic treatments are largely unsatisfactory. According to Barcelona Clinic Liver Cancer staging, the recommended treatment for HCC of an intermediate stage (B) is transcatheter arterial chemoembolization (TACE) [2]. However, the intermediate stage encompasses large heterogeneity in tumour size, number, location, and hepatic function. Although new chemotherapeutic agents have been developed, they still face many hurdles such as poor response rates, adverse events (AEs), and high overall costs. Although the benefits of locoregional versus systemic therapy remain controversial, locoregional therapy before systemic therapy is believed to be most effective for improving overall survival among non-surgically eligible patients [3].

Recent studies suggest that the combination of TACE and thermal ablation therapy is more effective than thermal ablation therapy alone [4–6]. However, these studies included patients with small (~ 3–5 cm), single tumours, whereas few studies have compared combination therapy versus TACE alone for intermediate-stage disease [7]. Also, the application of thermal ablation for large or multi-nodular HCC is technically difficult, as these types of tumours are prone to recur. Accordingly, few studies have evaluated local treatment for advanced-stage HCC. We postulate that combination of TACE and radiofrequency ablation (RFA) therapy could improve the rate of complete response (CR) and confer a survival benefit among patients with intermediate but beyond-the-Milan criteria. Although thermal ablation may not be applicable to large HCC, viable tumours after TACE are usually smaller than naïve tumours; thus, thermal ablation may also be applicable for viable tumours. The purpose of this trial is to compare 1-month tumour responses between patients with beyond-the-Milan HCC who receive combination TACE and RFA therapy versus TACE monotherapy.

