#### Allocation

One month after first TACE, patients with viable tumour as revealed by computed tomography (CT) will be randomly allocated into combination therapy or monotherapy groups on the morning of the day of second TACE.

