#### After allocation

All patients will undergo second TACE for the viable portion of the HCC with ethiodized oil and Gelfoam particles. Interventional radiologists performing second TACE will be blinded to patient allocation, and TACE will be performed in a conventional manner.

Patients in the combination TACE and RFA therapy group will be treated with additional RFA of the viable portion of the tumour under the guidance of fusion images from ultrasound and CT. RFA will be implemented within 1–2 days after second TACE. Whether RFA can be delayed for up to 1 month will depend on the medical condition of the patients. RFA will be performed by physicians at the three hospitals with more than 8 years of experience. A 17-gauge radiofrequency electrode system including three electrodes with a length of 150 mm and a 30-mm ablation zone (Octopus; STARmed, Goyang-si, Korea) will be used. The number of electrodes used will be determined based on the size of the viable tumour and the physicians’ discretion. However, physicians will attempt to obtain an ablation margin of at least a 1-cm perimeter around the viable tumour.

Patients in the TACE monotherapy group will be discharged from the hospital without further intervention if they experience no AEs.

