#### Outcomes {12}

The primary endpoint is 4–6-week CR in patients with viable tumour after first TACE. Tumour response rate will be evaluated in accordance with mRECIST [8]. In patients with multiple tumours, the sum of the largest diameters of viable lesions will be calculated.

Secondary outcomes include the following: (1) progression-free survival, defined as the time between random allocation and first progression; (2) overall response rate, defined as CR + partial response; (3) number of treatments (i.e., TACE) until achieving CR; (4) overall survival rate (i.e., 6, 12, and 24 months) and cause of death; and (5) change in liver function within 6 months based on liver function tests and Child–Pugh score.

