### Assignment of interventions: blinding

#### Who will be blinded {17a}

The interventional radiologist and patients will be blinded to patient allocation before second TACE and unblinded after second TACE. The independent outcome assessors will be blinded to patient allocation. The primary outcome (i.e., CR) will be assessed by comparing initial and follow-up MRIs.

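### The primary comparison of complete response is a valid but unadjusted chi-square that makes no use of viable tumour size at entry, a plausible predictor; adjusting for it would gain precision

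*Protocol article*

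**What the plan says.** The statistical methods section names the primary test without qualification: "For the primary endpoint, rate of CR will be compared using a chi-square test". Section {12} defines the endpoint: "The primary endpoint is 4–6-week CR in patients with viable tumour after first TACE". Response follows mRECIST, and for patients with several tumours "the sum of the largest diameters of viable lesions will be calculated".

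Viable tumour size is visible to the trial before allocation. Viable disease after the first TACE is an entry condition, and the Allocation section has it shown on CT about a month after that procedure. Size also enters treatment planning in the combination arm: "The number of electrodes used will be determined based on the size of the viable tumour" and on the physicians' discretion.

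Size appears nowhere in the design or analysis. Section {16a} stratifies randomisation by hospital only. Section {20b} plans subgroups by hospital and Child–Pugh score only. No adjusted analysis of CR is named.

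The article is not consistent about the baseline scan. The Allocation section and the timeline table use CT after the first TACE. Section {17a} says: "The primary outcome (i.e., CR) will be assessed by comparing initial and follow-up MRIs". The timeline also lists a baseline MRI at enrolment, but does not say whether it precedes or follows the first TACE.

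**The concern.** Whether a tumour disappears on imaging plausibly depends on how much of it was viable at the start. The protocol leans on this idea when it justifies ablation of the remnant: "viable tumours after TACE are usually smaller than naïve tumours; thus, thermal ablation may also be applicable for viable tumours". Its Background calls ablation of large or multinodular disease technically difficult, and its Discussion links high tumour burden to incomplete TACE. Eligibility admits single tumours of 5–8 cm, two of up to 8 cm and three of up to 5 cm, so entry size will vary.

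If size does predict CR, a test that ignores it leaves explainable variation in the error term. The stake is power in a trial with little to spare: 48 analysable patients per arm at the planned dropout. There is also an issue of timing. If the arms turn out to differ in size, an adjustment chosen after seeing that would be post hoc, so the decision has to be made in advance.

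**Working it through.** **Inputs.** From the sample size section {14}: CR 53% (combination) and 26% (TACE alone), two-sided α 0.05, 80% power, 48 per arm, 20% dropout, 60 per arm enrolled. The text calls the difference 28 points, but 53 − 26 = 27; I use 53% and 26%. The correlation ρ between entry diameter and CR within arms is not in the documents. It is assumed and varied.

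**1. The plan's own figure.** Unpooled formula: n = (1.960 + 0.842)² × [0.53×0.47 + 0.26×0.74] / 0.27² = 47.5, so 48 per arm. Dropout: 48 / 0.80 = 60. Both stated figures reproduce for an unadjusted comparison. (The pooled formula gives 50.3, so 51.)

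**2. Power of the planned chi-square.** Mean rate = (0.53 + 0.26)/2 = 0.395.
- SE under the null = √(2 × 0.395 × 0.605 / n)
- SE under the alternative = √((0.2491 + 0.1924) / n)
- Power = Φ[(0.27 − 1.960 × SE null) / SE alternative]

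At n = 48 the SEs are 0.0998 and 0.0959, z = 0.776, power 78.1%. At n = 60 they are 0.0893 and 0.0858, z = 1.108, power 86.6%.

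**3. Power with adjustment.** Adjusting for a covariate with correlation ρ multiplies the variance by about 1 − ρ², so both SEs are multiplied by √(1 − ρ²).

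| Assumed ρ | 48 per arm | 60 per arm |
|---|---|---|
| 0 (as planned) | 78.1% | 86.6% |
| 0.2 | 79.8% | 88.0% |
| 0.3 | 81.9% | 89.6% |
| 0.35 | 83.3% | 90.7% |
| 0.4 | 84.9% | 91.9% |
| 0.5 | 88.7% | 94.5% |

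A gain of 5 points needs ρ of about 0.35 at 48 per arm and about 0.4 at 60 per arm. A ρ of 0.35 corresponds to an odds ratio for CR of roughly 2.2 to 2.5 per SD of diameter.

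**4. Check by simulation.** 4,000 trials per setting, 53% versus 26%, one standardised covariate; chi-square against a logistic model with arm and size. Hospital was not simulated.

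| Log-odds of CR per SD of size | 48 per arm, unadjusted → adjusted | 60 per arm, unadjusted → adjusted |
|---|---|---|
| 0 (no relation) | 79% → 79–80% | 87% → 87% |
| 0.5 (weak) | 78% → 81% | 88% → 89% |
| 1.0 (moderate) | 78% → 85% | 87% → 92% |
| 1.5 (strong) | 79% → 90% | 86% → 95% |

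The simulation agrees with the formula. With no treatment effect and 48 per arm, the chi-square rejected in about 5% of trials and the adjusted tests in about 5–6%. A small part of the apparent gain is therefore finite-sample error, which a variance correction should address.

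**5. What chance imbalance looks like.** At 48 per arm, the difference in mean size between arms has SD √(2/48) = 0.20 baseline SDs, so 95% of trials lie within ±0.40. With the moderate covariate, an imbalance at that limit moves the expected unadjusted difference from 27 points to about 19 or 34. This is the same variation that step 3 counts as lost power, seen in a single trial.

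**The case against.** The case for leaving the plan alone is substantial. The chi-square is a valid test, the trial was sized for it, and the stated numbers reproduce. A reader might infer that ignoring size biases the comparison, or that chance imbalance is a second harm on top of lost power. Neither follows: randomisation makes imbalance symmetric, and the unadjusted standard error already allows for it.

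A reader might also take the protocol to establish that entry size predicts CR. It does not. The Background says a smaller remnant may make ablation applicable, which concerns feasibility in one arm. The Discussion's remark on tumours above 5 cm concerns original size, not the remnant. The relation is plausible but unmeasured, and for a weak one the gain is only about 1 to 3 points. Since the protocol states intention-to-treat and multiple imputation, 60 per arm may be nearer the analysed number than 48, and the gains there are smaller.

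Nor do the documents show that the entry diameter is already collected and the remedy is wording alone. No section lists it as a recorded item, the blinded central reading is described for response only, and the baseline scan is inconsistent.

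These objections set the size of the point but do not remove it. An unseen analysis plan might add a supportive adjusted model. But the article states the primary test itself, so an adjusted model there would remain secondary unless this text changes.

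**Conclusion.** The point holds as a matter of efficiency. The primary test is sound but forgoes a plausible predictor that can be measured on imaging already required before randomisation. Under assumed ρ from 0.2 to 0.5, adjustment adds about 1.7 to 10.6 points of power at 48 per arm (79.8 − 78.1; 88.7 − 78.1) and about 1.4 to 7.9 at 60 per arm (88.0 − 86.6; 94.5 − 86.6). With no size–CR relation there is essentially no gain and essentially no loss.

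These figures rest on 53% versus 26%, on ρ values the documents do not supply, and on the 1 − ρ² approximation, which the simulation supports. They do not show that the planned test is wrong or its estimate biased. The improvement is worth making because it needs no extra patients or scans, and because it can only be pre-specified before outcomes are compared. Recruitment is stated to run to about June 2026 and no interim analysis is planned, so there is time.

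**What to change.** Amend the protocol before the outcome comparison.

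1. Name the single pre-randomisation scan that supplies the entry diameter, reconciling the Allocation section and timeline table (CT after first TACE) with section {17a} (initial MRI).
2. Add the continuous sum of viable lesion diameters from that scan to the case report form.
3. In section {20a}, make the primary analysis a logistic model for CR with arm, that diameter (continuous) and hospital, the one stratification factor. Report the standardised CR risk difference with its confidence interval and test, using a small-sample variance correction.
4. Keep the unadjusted chi-square as a sensitivity analysis.

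Cost: a regression model with standardisation replaces a one-line test, and someone must read and record the entry diameter from the existing scan, including for patients already enrolled. No patients or scans are added.

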#### Sample size {14}

A previous study reports that the rate of CR after combination TACE and RFA therapy was 53% for patients with HCC tumours > 5 cm [9]. By contrast, the CR rate after TACE monotherapy was 26% for patients with intermediate-stage HCC [10]. Thus, we assume that the difference in CR rate between groups may be 28%. In this trial, we calculated that 48 patients per group are needed to achieve a two-sided α level of 0.05 and statistical power of 80%. A total of 120 patients will be included in this trial (i.e., 60 patients per group) to account for a 20% dropout rate (PASS, version 16, NCSS statistical software). Data will be analysed on an intention-to-treat basis according to patients’ originally assigned group.

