### Assignment of interventions: allocation

#### Sequence generation {16a}

An independent statistician will generate random numbers using STATA (ver. 16, StataCorp LLC) using a 1:2 to 1:6 random block stratified by three strata (i.e., hospitals). Data will be stored in a secure online database (i.e., REDCap) using electronic case report forms (e-CRFs).

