#### Methods for additional analyses (e.g., subgroup analyses) {20b}

Patient subgroups will be analysed according to treating hospital and liver function (i.e., Child–Pugh score).

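### The primary complete response test ignores the hospital strata used in randomisation; stratifying it costs nothing and recovers power if hospitals differ (minor)

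*Protocol article*

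**What the plan says.** Under Sequence generation {16a}, the allocation list uses a "random block stratified by three strata (i.e., hospitals"; Trial design {8} sets a 1:1 ratio.

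Under Statistical methods {20a}, the primary analysis is fixed: "For the primary endpoint, rate of CR will be compared using a chi-square test". For secondary endpoints that section names Kaplan–Meier analysis and log-rank tests, with no mention of strata. A general sentence covers other variables: "Independent sample *t*-tests or Mann–Whitney *U* tests for continuous variables", with chi-square or Fisher's exact tests for categorical ones.

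Hospital appears in the analysis only under additional analyses {20b}: "Patient subgroups will be analysed according to treating hospital and liver function (i.e., Child–Pugh score".

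The liver-function endpoint in Outcomes {12} is "change in liver function within 6 months based on liver function tests and Child–Pugh score". No test is assigned to it by name.

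**The concern.** A factor used to stratify randomisation would normally be carried into the main analysis. Balancing within hospitals removes between-hospital variation from the treatment contrast. The pooled chi-square still counts that variation in its variance. If hospitals differ in CR rate, the standard error is too large, the true significance level falls below 5%, and power is lost. The same reasoning applies to an unstratified log-rank test.

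This is not a detail left to an unseen analysis plan, because the protocol names the test and it does not match the design. At stake is a somewhat higher chance of missing a real effect.

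**Working it through.** **Inputs from the protocol.** Three hospitals, 1:1 allocation, two-sided 5% level, 80% power, 48 per group before and 60 per group after a 20% dropout allowance (Sample size {14}). Expected rates: "the rate of CR after combination TACE and RFA therapy was 53% for patients with HCC tumours > 5 cm" and "the CR rate after TACE monotherapy was 26% for patients with intermediate-stage HCC".

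**Reproducing the plan's figure.** For two proportions with unpooled variance, n = (1.960 + 0.842)² × (0.53×0.47 + 0.26×0.74) / 0.27² = 7.85 × 0.4415 / 0.0729 = 47.5, so 48 per group; 48 / 0.8 = 60. The sample size therefore rests on an unstratified comparison. (An aside: the protocol says "we assume that the difference in CR rate between groups may be 28" percent, but 53 − 26 = 27. With pooled variance, n is 47 for a 28-point difference and 51 for 53% against 26%.)

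**Why the unstratified test is conservative.** Under no treatment effect, let p_h be the CR rate in hospital h, w_h its share of patients and p̄ the overall rate. The pooled test uses a variance proportional to p̄(1 − p̄). With balance inside hospitals, the true variance is proportional to Σ w_h p_h(1 − p_h). With R the ratio of the second to the first, the true size is about 2[1 − Φ(1.96/√R)].

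Example with equal hospitals and null rates 62/38/18%: Σ w_h p_h(1 − p_h) = (0.2356 + 0.2356 + 0.1476)/3 = 0.206, and p̄(1 − p̄) = 0.395 × 0.605 = 0.239. Before rounding R = 0.864, so 1.96/√0.864 = 2.11 and the size is 3.5%. The simulated value is also 3.5%.

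**Simulation A: overall CR held at 26% vs 53%.** 40,000 trials per scenario, three equal hospitals. Hospital log-odds offsets of +s, 0, −s are an assumption. Size is at a common overall CR of 39.5%, 60 per arm.

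| s (control CR by hospital) | Power, 48/arm: chi-square / CMH | Power, 60/arm: chi-square / CMH | Size: chi-square / CMH |
|---|---|---|---|
| 0 (26/26/26%) | 78.2 / 77.9 | 86.9 / 86.8 | 5.1 / 5.0 |
| 0.5, mild (36/25/17%) | 78.5 / 79.2 | 87.2 / 87.5 | 4.7 / 4.9 |
| 1.0, marked (45/23/10%) | 79.8 / 83.7 | 88.3 / 90.6 | 3.5 / 5.0 |
| 1.5, extreme (53/20/5%) | 80.8 / 88.1 | 89.9 / 94.2 | 2.2 / 4.8 |

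With unequal hospitals (30/18/12 per arm) and the same offsets, power is 88.2 vs 90.3 for s = 1.0 and 89.5 vs 92.9 for s = 1.5.

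**Simulation B: common odds ratio 3.2, hospitals 30/18/12 per arm.**

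| Control CR by hospital | Power: chi-square / CMH | Size: chi-square / CMH |
|---|---|---|
| no differences | 86.8 / 86.7 | – |
| 20/28/38% (mild) | 85.1 / 85.4 | – |
| 15/30/50% (marked) | 79.8 / 82.4 | 4.2 / 5.0 |
| 10/35/60% (extreme) | 68.9 / 77.2 | 3.1 / 4.9 |

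Only the gap within a row measures the choice of test. The fall down the chi-square column mostly reflects a smaller overall effect: in the last row the overall rates are about 27.5% and 48.7%, a difference of about 21 points rather than 27. In that last scenario at 48 per arm (24/14/10), power is 57.5 vs 67.3.

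**Liver function (secondary).** With equal variances at baseline and follow-up and correlation r, the ANCOVA variance divided by the change-score variance is (1 − r²)/[2(1 − r)] = (1 + r)/2. For r = 0.3, 0.5, 0.7 and 0.8 this is 0.65, 0.75, 0.85 and 0.90, a saving of 35%, 25%, 15% and 10%. The documents give no value of r.

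**The case against.** The strongest reply is that hospital differences are assumed. The protocol requires RFA operators with more than 8 years' experience, names one electrode system, places all three hospitals in one university, and has CR read by independent blinded radiologists. RFA operators act only in the combination arm, so operator differences would mainly make the treatment effect vary rather than spread the control rates. This stands: the protocol documents no CR differences. It does leave room for some, since electrode number and the first TACE agent are local decisions and recruitment is competitive, and it plans its own look at results by hospital. That subgroup look does not replace a stratified primary test.

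Three stronger readings are tempting and not supported.

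- A reader might infer that the mismatch invalidates the primary test. It does not. The error is conservative: simulated size stayed at or below about 5%.
- A reader might infer that the trial has no power to spare, from the 78% at 48 per arm. That is the size after dropout. The protocol states intention-to-treat with 60 per arm and plans multiple imputation, and at 60 power is about 87% when hospitals are alike. The section on non-adherence {20c}, which leaves some data out, makes the effective number uncertain, so both sizes are shown.
- A reader might infer that liver function is compared without its baseline. The endpoint is a change, so baseline already enters by subtraction. Only its use as a covariate is absent. Both analyses are valid under randomisation, and the choice could fairly be left to the analysis plan.

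**Conclusion.** The point holds as a minor one: the protocol fixes a primary test that does not reflect its stratification factor. At 60 per arm, stratifying gains about nothing with no or mild hospital differences (under half a point), 2 to 3 points with marked ones and 3 to 8 with extreme ones. At 48 per arm the gains are just under 4 points with marked differences (equal hospitals) and about 7 to 10 with extreme ones. If hospitals do not differ, stratifying costs 0.1 to 0.3 points.

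The scenarios for hospital rates and hospital sizes are assumptions. The consequence is a possible missed effect and an interval wider than needed if it is built on the same pooled variance. For the log-rank tests the argument is the same in kind, and no size is claimed. The ANCOVA gain is optional and depends on an assumed correlation.

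**What to change.** Amend Statistical methods {20a} so that:

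- the primary comparison of CR is a CMH test stratified by hospital, reported with the hospital-stratified difference in CR rate and its 95% CI;
- the log-rank tests for progression-free and overall survival are stratified by hospital;
- the simple chi-square is kept as a sensitivity analysis;
- optionally, 6-month Child–Pugh score is analysed by ANCOVA with baseline score and hospital as covariates.

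The cost is wording in the protocol or analysis plan. Hospital and baseline Child–Pugh score are already needed for randomisation and the endpoint, so no new data are required. The protocol describes recruitment as ongoing and plans no interim analysis, so the change can be pre-specified before outcomes are compared by arm.
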